#### Data analysis

Descriptive summaries of outcomes, by time point, as well as simple pre-post comparisons (mean difference with two-sided 95% confidence interval) will be produced using Stata or R software. Contexts will be assessed per FGC, from a combination of family and practitioner questionnaire data. Additional analyses will involve fitting two-level regression models with random family effects to study the interplay of multiple contextual and implementation factors per follow-up time-point and longitudinally, as well as outcome variability between family members attending the same FGC. Fixed effects will include time-point, contextual/implementation factors, and possibly time-by-contextual factor interaction terms. Examples of possible contextual and implementation factors would be family size, stage of the child welfare process (e.g., early help, child in need, edge of care) and local authority culture, as assessed by family and practitioner (possibly a scale measure). Estimates of the effects of contextual factors will be presented with two-sided 95% confidence intervals and p-values.

Data from the WP2 family survey data a few weeks after FGC will be used to assess the reliability and validity of outcome measures by repeating or extending some of the original validation work on key measures, particularly where they have been adapted for use in this study, using e.g., Cronbach’s alpha, criterion validation and examination of factor structure and ceiling and floor effects. A statistical analysis plan will be developed to cover both WP2 and WP3.

Semi-structured interviews will be coded in NVivo software, using thematic analysis31. The coding frame will be developed through a combination of the programme theory from WP1 and inductive initial analysis of interview transcripts, with context, mechanisms and outcomes featuring as analytic codes.

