### Work Package 2: Prospective single-arm study of FGC variability and outcomes after six months (RQ3)

Public-facing title: Family views and context study (Family VOICE project)

WP2 considers process and short- and medium-term outcomes of FGCs, using evaluation tools (questionnaires) co-designed with families and practitioners in WP1. A questionnaire will be used with FGC participants, before, a few weeks after, and six months after an FGC.

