Having consulted results from comparative studies of family group decision-making that have measured empowerment at later time points [33–35], it is possible to estimate a sample size for comparing different kinds of FGC (e.g., early help vs. edge of care–contexts where the level of empowerment could be quite different). To detect a 0.25 difference between two groups of equal size on a five-point scale, with a standard deviation of 0.50, 95% confidence and 80% power, a sample size of 128 families will be required (two-sample t-test). For a pre-post comparison to estimate the mean improvement from baseline to six months in all FGC participants, N = 128 will allow us to detect a minimum effect size of 0.125 with 80% power, or a minimum of 0.144 with 90% power (one-sample t-test). Assuming a 36% attrition rate between the first questionnaire and six-month follow-up, which is conservative in light of the same rate having been found by Dijkstra et al. over a 12-month follow-up period [34], an initial sample size of 200 FGCs will be needed. The current English trial of FGCs at pre-care-proceedings stage 6 shows an average of 73 conferences a year planned in each of the 24 participating local authorities, so for a minimum of 128 families to participate in the full survey across several different services seems feasible.

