#### Data analysis

We will use Stata or R software to estimate a family’s propensity for having an FGC with a logistic regression on variables including stage of the child welfare process (referral, child in need, child protection assessment, child protection plan), reason for referral and family demographics. The analysis model for the primary outcome variable (whether the level of social care intervention at two years after the FGC–or equivalent baseline date for the control group–has increased or not) will be two-level logistic regression, with random effects for local authorities and weighting of families according to their propensity for having an FGC. Fixed effects will include intervention (whether a family has had an FGC or not) as well as other factors–to be determined in WP1 –to account for the different ways FGCs are set up in different local authorities. Effect estimates will be presented with two-sided 95% confidence intervals and p-values. Secondary outcomes will be analysed using the same propensity score weighting approach and appropriate two-level regression models depending on the type of outcome variable (e.g., logistic for binary outcomes, linear for continuous outcomes).

We will undertake multiple imputation to explore the impact of potential missing data. We will also consider alternative covariate balancing or matching methods, such as entropy balancing [43], Mahalanobis distance matching [44] and coarsened exact matching [45] if propensity score weighting does not achieve good enough covariate balance and/or as sensitivity analyses. Detailed statistical analysis plans for WP2 and WP3 will be finalised prior to any analysis being performed, and these will be published on the study website.

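### WP2's longitudinal two-level model leaves out the person and service levels, and WP3 does not say whether the analysed row is a child or a family

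*Protocol article*

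**What the plan says.** **WP2, Data analysis.** The additional analyses consist of "fitting two-level regression models with random family effects to study the interplay of multiple contextual and implementation factors per follow-up time-point and longitudinally". The same sentence says they will examine "as well as outcome variability between family members attending the same FGC", so individual members' scores enter the model. "Fixed effects will include time-point, contextual/implementation factors, and possibly time-by-contextual factor interaction terms". Examples of contextual factors are family size, "stage of the child welfare process (e.g., early help, child in need, edge of care) and local authority culture"; the last of these is described as "local authority culture, as assessed by family and practitioner (possibly a scale measure". Estimates are to carry 95% confidence intervals and p-values.

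**WP2, opening section.** "A questionnaire will be used with FGC participants, before, a few weeks after, and six months after an FGC". Each person can therefore contribute three records.

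**WP2, Sampling, settings and research participants.** Any willing FGC service may join, and variation both within and between services is what will let context be studied. The number of services is not fixed. The planning calculation takes one composite empowerment score per FGC and concludes that "a sample size of 128 families will be required (two-sample t-test").

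**WP3.** The primary model "will be two-level logistic regression, with random effects for local authorities and weighting of families". Exposure, eligibility and the sample size (300 and 1000) are expressed in families. The escalation ladder describes the status of the child, and Data collection and linkage says that children are followed up for two years.

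**The concern.** The random-effects structure decides which comparisons are treated as precise. With a family intercept only, one person's three questionnaires are taken to be no more alike than questionnaires from two relatives. Stable differences between persons then go into the residual, and the time effect is judged against too much noise.

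The missing service level works the other way. A factor that is constant within a service is compared across a handful of services, but the model counts families as the independent units, so its interval is too narrow if services differ. RQ3 asks how variation in quality and implementation affects outcomes, and some of that variation lies between services. The WP3 model has a random effect for local authorities, so the plan recognises this kind of clustering there but does not carry it into WP2.

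In WP3 the difficulty is one of definition. Exposure belongs to a family and the outcome to a child, and the article gives no rule for families with more than one child.

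**Working it through.** **1. The plan's own figures.** For a difference of 0.25 and SD 0.50 (standardised 0.5), two-sided 5% and 80% power, the two-sample t-test needs 63.8 per group, so 64 per group and 128 in all. Attrition: 128/(1 − 0.36) = 200. For the pre-post comparison, the detectable change with 128 families is 0.125 at 80% power and 0.144 at 90%, on the SD 0.50 scale. All agree with the article.

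**2. Assumptions for the model check (none is in the document).** 128 families, m = 3 members, T = 3 time-points, 8 services of 16 families, total variance 1, family variance 0.20. Person (vp), occasion (ve) and service (vs) variances vary as shown.

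**3. Time effect.** A model with family effects only estimates a pooled within-family residual

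w = [(m − 1)(ve + T·vp) + m(T − 1)·ve] / (mT − 1),

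whereas a time contrast truly has residual ve. The reported SE divided by the true SE is √(w/ve).

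- vp 0.40, ve 0.40: w = (2 × 1.6 + 6 × 0.4)/8 = 0.70; √(0.70/0.40) = 1.32
- vp 0.20, ve 0.55: w = (2 × 1.15 + 6 × 0.55)/8 = 0.70; √(0.70/0.55) = 1.13

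The time effect's SE is too large for any non-zero person variance. Time-by-context interactions use the same residual and are affected in the same way.

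**4. Service-level factor (4 services against 4).** Let f = vf + vp/3 + ve/9, the variance of a family mean excluding service. The model reports variance 2(f + vs)/64; the true variance is 2(vs/4 + f/64).

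| vs | vp | ve | f | reported SE | true SE | ratio |
|---|---|---|---|---|---|---|
| 0 | 0.40 | 0.40 | 0.378 | 0.109 | 0.109 | 1.00 |
| 0.02 | 0.38 | 0.40 | 0.371 | 0.111 | 0.147 | 0.75 |
| 0.05 | 0.35 | 0.40 | 0.361 | 0.113 | 0.190 | 0.60 |
| 0.10 | 0.30 | 0.40 | 0.344 | 0.118 | 0.247 | 0.48 |

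**5. FGC-level factor balanced within services.** Reported over true SE = √[(f + vs)/f], which is 1.00, 1.03, 1.07 and 1.14 for the same four rows. With no service variance the ratio is exactly 1, so the missing person level does no harm here.

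**6. Simulation check.** Fitting the stated model 200 times to data with vs 0.05, vf 0.20, vp 0.35 and ve 0.40 gave SE ratios of 1.23 (time), 1.08 (FGC-level factor) and 0.60 (service-level factor). Rejection under the null at a nominal 5% was 1.5%, 3.0% and 26%.

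**7. Power with 128 families for a factor constant within services.** Design effect = 1 + (16 − 1) × ICC; effective n per group = 64 divided by this.

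- ICC 0.02: 1.30, n = 49.2, power 69%
- ICC 0.05: 1.75, n = 36.6, power 56%
- ICC 0.10: 2.50, n = 25.6, power 42%

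These are somewhat optimistic, since they do not reduce the degrees of freedom to reflect 8 services.

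**8. WP3, only if rows are children.** With 1.5 to 2.5 children per family and a within-family ICC of 0.3 to 0.8 (assumed), the design effect 1 + (m − 1) × ICC runs from 1.15 to 2.20. The unadjusted SE is then 1/√1.15 = 0.93 to 1/√2.20 = 0.67 of the true SE. If rows are families, the design effect from siblings is 1.

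**The case against.** The case on the other side is substantial, and much of it stands.

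- **Where the person level matters.** At a single time-point the person is level 1 within the family, and the model is complete. If one composite per family is used, as the sample-size section assumes and the co-design phase may yet choose, occasions within families is also complete. The gap exists only for individual scores analysed longitudinally. The stated aim of studying variability between members makes that analysis a real part of the plan.
- **False positives for context factors in general.** A reader might infer that the missing person level inflates error rates for RQ3 broadly. It would do so for a covariate that differs between members of one family, but contexts are to be assessed per FGC and none of the listed examples is of that kind. Main effects of FGC-level factors are not distorted.
- **Simple pre-post change and the 128-family calculation.** A reader might think clustering of relatives invalidates both. With random intercepts, family and person effects cancel in change scores, and the sample-size calculation has one score per family. Only the service question bears on the t-test.
- **Stage and culture as service-level factors.** The article expects variation within as well as between services, and culture is rated by family and practitioner. These factors may vary within services, in which case the service-level loss does not apply to them in full.
- **A missing family level in WP3.** This is a tempting reading, but the model weights families and defines exposure by family. Families within authorities is a complete two-level structure. Only child rows would lack a level, and the error would then run one way.
- **Detail for the analysis plan.** WP2 is exploratory, its outcomes are still to be chosen, and an analysis plan is promised. However, the article does not leave the structure open: it names two levels and family effects and applies them longitudinally. A plan that followed that wording would give wrong standard errors.

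**Conclusion.** The point holds for WP2 in a limited form. The stated model is mis-specified for longitudinal analysis of individual scores, and it has no service effect. Time effects are reported with SEs about 1.1 to 1.3 times too large, which costs power. Service-level factors are reported with SEs of about 0.75 to 0.48 of the true value if services differ, and correctly if they do not. The 80% power claim holds for factors varying within services and falls for factors varying between them, for example to about 56% with 8 services of 16 families and ICC 0.05.

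The direction for the time effect needs only some person-to-person variance. The direction for service-level factors needs some variance between services. Every size rests on assumed variance components, family size and number of services.

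For WP3 the firm finding is that the unit of analysis is not stated: family for exposure, weights and sample size, child for outcome and follow-up. It does not follow that the WP3 model lacks a level.

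**What to change.** **WP2.**
- In the longitudinal model of individual scores, add a random intercept for person within family.
- In all WP2 models, add a service effect: random, or fixed if services are few and only factors varying within services are of interest.
- Say that 128 families gives 80% power for factors varying within services, and give the lower power for factors varying between services under a stated ICC and number of services.

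**WP3.** State the row.
- If it is the child, add a family random effect or family-clustered variance.
- If it is the family, define the outcome by an index-child or worst-sibling rule that works identically in FGC and comparison authorities. Choosing the child for whom the FGC was held would not do, because comparison families have no such child.

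**Cost.** A few sentences in the analysis plan, slightly longer model fitting, and wider intervals for service-level factors. No additional data collection is needed beyond keeping person, family and service identifiers.

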### Work Package 3: Comparison of service use and associated costs in FGC participants and a comparison group after two years using a quasi-experiment (RQ4)

Public-facing title: Service use study (Family VOICE project)

WP3 is a quasi-experiment to assess service use outcomes of FGCs and the economic dimension of these. The experimental dimension is comparison of families who have had FGCs with similar families in local authorities with no FGC provision. This work package will assess some longer-term outcomes from the programme theory developed in WP1 for which administrative data are more suitable than self-report, because of the need for complete coverage of the relevant population without social desirability bias.

Outcomes to be measured include:

1. Primary outcome

The primary outcome is whether category (of seriousness) of children’s social care intervention at two years after FGC (or equivalent date for comparison group) is the same level, lower or higher than at the time of FGC. A ladder of escalation will be used, with state intervention categories ordered from most to least serious, including the child having been:

categorised as in need (and reason for this);subject to a child protection investigation;on a child protection plan;looked after by the local authority (and, if so, on what legal basis; type of care–foster, kinship, residential, placed with parents).

The primary outcome variable will be binary, describing whether the category of statutory intervention at 2 years after FGC (or equivalent date for the non-FGC group) is the same or lower than at the time of FGC (or equivalent date) or whether it is higher.

2. Secondary outcomes

Highest category of children’s social care intervention since the FGC (or equivalent date for comparison group) at any time during the two-year follow-up.

A summary measure of duration and seriousness of all children’s social care intervention during follow-up.

Health care use for health conditions and events which might potentially be affected by FGC attendance–e.g., child and parent mental health, serious injury to a child, assault resulting from domestic abuse:

hospital admissions;outpatient appointments;‘Improving Access to Psychological Therapies’ [39] services;community mental health services;accident and emergency attendances.

Absence from school and special educational needs provision.

Incremental cost per adverse social-care-outcome-adjusted year avoided.

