#### Sampling, settings and research participants

Families who have attended FGCs will be identified by local authorities–we will work with several large authorities in England, and access anonymised data from the Department for Education, NHS Digital and the Office for National Statistics (ONS). This part of the study is not linked in any way to the WP2 families. In these participating local authorities, we will also access routine data on families who have been referred to children’s services but have not had an FGC, in order to delineate the circumstances in which families do and do not take part in FGCs in these particular authorities.

A comparison group of local authorities which do not offer FGCs will be identified in the WP1 survey. Families from these authorities will be identified from the Children in Need Census. This part of the study uses data from only one UK country–England–because the datasets are different for each nation and given the complexity of data linkage it would not be feasible to attempt this study in more than one nation. We have chosen England as having the largest population.

Eligible families will be those with at least one child under 18 years of age referred to departments of Children’s Social Care Services from 1.1.17 to 31.12.19 at participating local authority sites in England (there is no intention to connect these local authorities to those taking part in earlier work packages). No additional exclusion criteria will be applied. At this stage we are not imposing a lower age limit. However, although we are confident that linkage to health records for school-age children is viable, there is some uncertainty about this linkage for pre-school children. We will therefore have to test the feasibility of extending the age profile to include all children from birth, in the early stages of WP3.

To make the two groups of families from different local authorities comparable for analysis, we will use statistical techniques to improve balance across the two groups for several known confounders. We will use propensity score weighting [40, 41] to estimate the average ‘causal’ effect of having an FGC on the outcomes.

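### WP3's binary primary outcome cannot show escalation for children already looked after at baseline, and the propensity stage variable as listed omits that category

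*Protocol article*

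**What the plan says.** **Outcome.** The opening section of WP3 in the protocol article defines the primary outcome on a ladder of "state intervention categories ordered from most to least serious, including the child having been" in one of four categories. The list starts at child in need, passes through child protection investigation and child protection plan, and ends with "looked after by the local authority (and, if so, on what legal basis", where type of care is also recorded. The introductory words give the opposite order to the list, but looked after is plainly meant as the most serious category. The ladder is then reduced to two values: whether the category at two years "is the same or lower than at the time of FGC (or equivalent date) or whether it is higher".

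**Who is in.** WP3, Sampling, settings and research participants, admits families with "at least one child under 18 years of age referred to departments of Children’s Social Care Services from 1.1.17 to 31.12.19" and adds: "No additional exclusion criteria will be applied".

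**Weights and model.** WP3, Data analysis, bases the propensity score on variables that include "stage of the child welfare process (referral, child in need, child protection assessment, child protection plan", with reason for referral and family demographics. The outcome model is a propensity-weighted two-level logistic regression with a random effect for local authority. Its named fixed effects are FGC status and factors for how FGCs are set up locally. Baseline rung is not among them.

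**The concern.** Escalation needs somewhere to escalate to. A child on the top rung at the index date has none, so that child's outcome is settled before follow-up begins. One who returns home and one who stays in care for the whole two years are both coded the same or lower.

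This would matter less if the analysis set these children aside or balanced on their status. As written it does neither. Eligibility keeps them in, and the listed stage variable has no level for them, although being looked after determines the outcome completely.

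Two things are at stake:

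- **Dilution.** Children who cannot escalate pull both groups' rates towards zero and shrink the difference between them.
- **Bias, if the shares differ.** If looked-after children are more common in one group after weighting, that group shows less escalation for reasons unrelated to FGCs.

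The share looked after at baseline also depends on the index date, which is not consistent. The outcome definition counts from the FGC, or an equivalent date for the comparison group. WP3, Data collection and linkage, counts two years from referral. FGC families may move up the ladder between those dates.

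**Working it through.** **Inputs from the protocol** (WP3, Sampling): 300 FGC families, 1000 comparison families, a detectable difference of 10.5 percentage points, proportions around 0.5, 90% power, 95% confidence (taken as two-sided).

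**Inputs not in the protocol** (assumed): q, the share of analysed units already looked after at the index date; r, the escalation rate among those below the top rung.

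**1. The plan's own figure.** The two-sample test for proportions uses a pooled standard error under the null (SE0) and an unpooled one under the alternative (SE1):

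power = Φ[(d − 1.96 × SE0) / SE1]

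For 0.4475 against 0.5525, d = 0.105, SE0 = 0.0329 and SE1 = 0.0327, so power = Φ(1.24) = 89.3%. Solving at proportions of 0.5 gives (1.960 + 1.282) × √[0.25 × (1/300 + 1/1000)] = 10.7 points. The stated 10.5 is reproduced to within rounding.

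**2. Dilution, equal shares.** If a share q in each group cannot escalate, both rates, and so their difference, are multiplied by (1 − q). Start from 0.4475 against 0.5525 among children able to escalate.

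| q | Rates, all children | Difference (points) | Power, all children | Power, restricted to those able to escalate |
|---|---|---|---|---|
| 0% | 0.4475 vs 0.5525 | 10.5 | 89.3% | 89.3% |
| 5% | 0.425 vs 0.525 | 9.98 | 86.0% | 87.7% |
| 10% | 0.403 vs 0.497 | 9.45 | 82.3% | 85.9% |
| 20% | 0.358 vs 0.442 | 8.40 | 73.8% | 81.6% |

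Restriction brings back the 10.5-point contrast but uses fewer families (270 and 900 at q = 10%). By the formula in step 1, its detectable difference is then 11.3 points at 10% and 11.9 at 20%.

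**3. Bias, unequal shares.** With no true effect among children able to escalate:

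spurious difference (FGC − comparison) = r(1 − q_FGC) − r(1 − q_comp) = −r(q_FGC − q_comp)

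| r | q FGC | q comparison | Spurious difference (points) |
|---|---|---|---|
| 50% | 10% | 2% | 45.0 − 49.0 = −4.0 |
| 50% | 2% | 10% | 49.0 − 45.0 = +4.0 |
| 30% | 10% | 2% | 27.0 − 29.4 = −2.4 |
| 50% | 20% | 5% | 40.0 − 47.5 = −7.5 |
| 50% | 5% | 20% | 47.5 − 40.0 = +7.5 |
| 20% | 20% | 5% | 16.0 − 19.0 = −3.0 |
| any | equal | equal | 0 |

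A negative value looks like benefit from FGCs, a positive one like harm. The power figures ignore clustering and the loss of effective sample size from weighting.

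**The case against.** The best defence is that the text leaves room. The ladder categories and the propensity variables are both introduced as inclusive lists, so a looked-after level could be added, and legal basis or type of care could be ranked into sub-rungs that lift the ceiling. Other balancing or matching methods are planned if balance is poor. A secondary outcome summarising duration and seriousness of intervention could register change in children already in care. Elsewhere the protocol mostly describes FGCs held before care (early help, child in need, edge of care, pre-proceedings), so the looked-after share may be small. The 10.5 points is a detectable difference for a generic worst case, already said to grow under weighting. It is not an assumed effect among children able to escalate.

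Much of this stands, and it limits the size of the problem. It does not remove it. The stage levels are spelled out and stop one rung short, no ranking within looked after is given, balance checks on the listed variables would not reveal imbalance in an unlisted one, and a secondary outcome does not repair the primary.

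Two stronger readings are tempting, and the protocol supports neither.

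- **That the primary estimate is biased in favour of FGCs.** This needs a higher looked-after share in the FGC group after weighting. No share is given for either group, and the reverse imbalance gives the opposite sign.
- **That young people who turn 18 within two years are counted as not higher.** Eligibility does run to "at least one child under 18 years of age", so some will reach 18 before the endpoint. But no coding is stated. They could be treated as missing, censored or excluded, and such a rule normally belongs in the statistical analysis plan, which is not at hand.

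**Conclusion.** The point holds as a defect in how the primary outcome, eligibility and propensity variables fit together. On the ladder as listed, children looked after at baseline have a predetermined outcome, nothing removes them, and the listed weights do not separate them.

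Dilution follows from any such share: at an assumed 10% to 20% in both groups, 10.5 points becomes about 9.5 to 8.4 and power falls from about 90% to about 82% to 74%. Bias is conditional on unequal shares after weighting and can go either way; 4.0 points for 10% against 2% at 50% escalation is an illustration. All of these rest on assumed shares, treated as shares of analysed units. The protocol samples and weights families but defines the ladder for a child, so a share of children need not equal a share of families.

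**What to change.** Before the analysis plan is finalised:

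1. Add a looked-after level to the propensity stage variable so that it covers every ladder rung. The secondary outcomes use the same weighting approach and need it too.
2. Define the at-risk set for the primary escalation analysis as children below the looked-after rung at the index date, and include baseline rung as a fixed effect. The restriction is needed as well as the adjustment: a looked-after level in the logistic model would contain no escalations, so its coefficient could not be estimated.
3. Analyse children looked after at baseline separately, as still looked after or not at two years.
4. State the ladder order the right way round, say whether legal basis or type of care forms ranked sub-rungs, and reconcile the index date between the outcome definition and the data linkage section.

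An ordinal outcome or explicitly ranked sub-rungs would be an alternative to the restriction if the full population must stay in the primary analysis.

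The cost is mainly wording. The primary sample becomes somewhat smaller and the target population narrower. Restriction restores the contrast but not the full 90% power: about 86% if 10% are excluded and about 82% if 20% are, before clustering and weighting. The children set aside carry no information on escalation as the ladder stands.

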A realistically achievable sample size of 300 families who have had an FGC and 1000 ‘control’ families in local authorities that do not offer FGCs would allow for the detection of a difference of 10.5 percentage points between groups for a binary outcome in a ‘worst-case scenario’ (i.e. proportions around 0.5) with 90% power and 95% confidence (two-sample test for proportions), but since propensity score weighting tends to shrink the ‘effective’ sample size the minimum detectable difference will be somewhat larger.

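### The first WP3 secondary outcome, highest category since the FGC, is not referenced to the category held at the FGC, so prevented escalation is diluted by starting severity and precision is lost

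*Protocol article*

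**What the plan says.** In the Protocol article, the Work Package 3 outcome list orders statutory categories on a ladder from child in need up to looked after. The primary outcome is binary and referenced to baseline: whether the category at two years "is the same or lower than at the time of FGC (or equivalent date) or whether it is higher". The first secondary outcome drops that reference: it is the highest category "since the FGC (or equivalent date for comparison group) at any time during the two-year follow-up". No sentence says whether a category already in force on the index date counts.

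Under Data analysis, the propensity model uses "stage of the child welfare process (referral, child in need, child protection assessment, child protection plan), reason for referral and family demographics". For the other outcomes, "Secondary outcomes will be analysed using the same propensity score weighting approach and appropriate two-level regression models depending on the type of outcome variable". Baseline category is not named as a covariate in the outcome model for secondary outcomes. Detailed analysis plans are to follow and are not shown.

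**The concern.** Every rung is a status with duration. A child on a protection plan at the FGC is still on it the next day, so the highest category from then on is at least a plan. Three children then score alike: one who leaves the plan after a week, one who stays on it for two years, and a child in need who escalates to a plan. Only moves above baseline can differ because of the FGC, and they are read against the full spread of starting severity.

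The primary outcome looks at a single date and misses escalation that has reversed by two years. This secondary outcome is the one that could show it, so a loss of sensitivity here matters more than its rank suggests.

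**Working it through.** **The plan's own figure.** The sample is "300 families who have had an FGC and 1000 ‘control’ families in local authorities that do not offer FGCs", said to allow "detection of a difference of 10.5 percentage points between groups for a binary outcome" with 90% power and proportions near 0.5. With unpooled variance, control 0.5 and FGC 0.605:

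(1.960 + 1.282) × √(0.25/1000 + 0.605 × 0.395/300) = 3.242 × 0.03235 = 0.1049, or 10.5 points.

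The figure reproduces and is not in question. It is for a generic binary outcome; no figure is given for highest category.

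**Assumed inputs (the documents give none).** Four rungs scored 1 to 4, with the index-date category carrying into follow-up. A rise occurs in 30% of control and 20% of FGC children below the top rung. Families are independent.

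**One case by hand, unweighted.** Baseline mix 40/20/30/10%, one-step rises.

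- Children below the top rung: 90%. Rise: 0.9 × 30% = 27% v 0.9 × 20% = 18%. Mean highest category therefore falls by 0.09. The effect is present in the raw outcome.
- SD of the raw highest category: 1.083. SD of highest minus baseline: √(0.27 × 0.73) = 0.444.
- Standard error = SD × √(1/300 + 1/1000) = SD × 0.0658, giving 0.0713 raw and 0.0292 relative to baseline.
- z = 0.09/0.0713 = 1.26 and 0.09/0.0292 = 3.08.
- Power = Φ(1.26 − 1.96) = 24% raw and Φ(3.08 − 1.96) = 87% relative to baseline.

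**With the planned kind of weighting, by simulation.** Controls are weighted to the FGC group's baseline category, with exact balance. Baseline mixes are 60/10/25/5, 40/20/30/10 and 25/10/50/15%. A rise goes either to a random higher rung or up one step. Ranges are across mixes.

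| Analysis | Power |
|---|---|
| Raw highest category, weighted, conventional standard errors, random rise | 27-56% |
| Same, one-step rise | 2-8% |
| Any rise above baseline, weighted | 89-94% |
| Highest category adjusted for baseline category | 82-95% |

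In these scenarios highest category equals starting category in about 72-75% of controls. Baseline explains about 48-63% of its variance (random rise) or 82-83% (one-step rise).

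**Why weighting alone does not help here.** Exact balance steadies the estimate, but a conventional standard error (weights taken as fixed) still contains the baseline spread. In the hand case significance needs a difference of 1.96 × 0.0713 = 0.140. The estimate centres on 0.09 with a true spread of roughly 0.029, so it must lie (0.140 − 0.09)/0.029 = 1.7 SDs above its mean, a chance of about 4%.

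**Check for false positives.** With no FGC effect and a 5-point raw imbalance in the share on a plan, the weighted raw outcome rejects in 0-1% of runs with conventional standard errors and 4-6% with a variance stratified by baseline category.

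**The case against.** The strongest reply is that baseline stage is already in the propensity model and the same weights apply to secondary outcomes. That largely stands against a charge of bias. A reader might infer that this outcome could show an FGC effect that is only baseline imbalance. Without weighting it could, but the plan weights on that variable and the false positives then disappear where balance is achieved. The remaining caveat is small: the stages listed for the propensity model do not name looked after, the top rung.

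A reader might also infer that prevented escalation is hidden. It is not: a child who would have risen and did not has a lower maximum. What a maximum cannot show is de-escalation, and an any-rise measure cannot show it either. The next listed secondary outcome, on duration and seriousness of all intervention, separates a one-week plan from a two-year plan.

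The reply is also right that a variance respecting the weighting recovers most of the power: 83-88% for weighted mean highest category under random rises. The loss therefore depends on the standard errors used, which the protocol does not fix. Finally, carry-over of the index-date category is implied, not stated, and a counting rule could sit in the unseen analysis plan. But the protocol itself sets this outcome in a different frame from the primary one, so the choice of reference is more than omitted detail.

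**Conclusion.** The point holds as a matter of precision in one secondary outcome. On the natural reading the baseline category is a floor and starting severity makes up much of the outcome's spread. Under the assumed 30% v 20% rise, power is about 2-56% for the weighted raw outcome with conventional standard errors, against about 82-95% once it is referenced to or adjusted for baseline category. These figures illustrate a range. They rest on assumed mixes and rise rates, four rungs, exact balance on baseline category and no clustering by local authority. How far real scores would reflect starting severity cannot be established from the documents. The primary outcome and the 10.5-point calculation are unaffected.

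**What to change.** Reference this outcome to the index-date category in one of two ways, and state whether a category open on that date counts.

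1. Test whether the child's category rose above the one held at the FGC (or equivalent date) at any time in the two years, counting only categories that start after that date. Tabulate the highest rung by baseline category as description. Treat children already on the top rung as in the primary outcome.
2. Keep highest category and add baseline category as a covariate in its weighted two-level model.

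Both use the same linked records. The first gives up a formal test of how far a child escalated. The second keeps that test and costs one extra model term. Either can be written in before the analysis plan is finalised.
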